### Study adherence and withdrawal

#### Assessment of adherence

Outcome data will be collected remotely whenever feasible by participant completion of postal or secure web-based questionnaires. This will be supplemented by e-mail or text alerts to participants notifying the need to complete questionnaires with additionally up to two reminders in these formats for non-responders. Local research staff will make use of planned routine clinical visits, whether for the underlying health condition or urinary tract monitoring, to check completion of trial documentation and collect clinical outcome information such as urine and perianal swab specimens. Participants allocated to prophylaxis will be contacted after 1 month to assess tolerability and if necessary allow change to alternative agent with re-checking of tolerability after a further month. We will assess adherence to the allocated arm (prophylaxis or no prophylaxis) by 3-monthly contact with the participant to check tolerability and surveillance of their primary healthcare record to record issuing of relevant prescriptions and consultations involving discussion of UTI treatment. We will contact participants more frequently if they need assistance to complete trial documents, particularly the UTI log.

All information will be recorded in the relevant CRF. If we do detect change from allocation, we will explore and record the reasons for this with the participant and the relevant clinician. Wherever possible these participants will remain on study and continue collection of planned outcome information. Trial literature will emphasise the need to adhere to the allocated strategy during the 12-month trial period if possible and will record any deviation. Multiple switching between prophylactic agents will be allowed. Previous studies suggest that this will affect approximately 12 % of participants [26], although a higher rate was seen in children (48 %) [27]. The trial statistician will monitor attrition rate against our anticipated maximum of 15 % and report to the TSC and DMC.

#### Withdrawal of participants

Participants have the right to withdraw from the study at any time for any reason, and without giving a reason. The investigator will also withdraw patients from the study intervention if it is judged to be in the patient’s best interests. It is understood by all concerned that an excessive rate of withdrawals can render the study uninterpretable; therefore, unnecessary withdrawal of patients should be avoided. Should a patient decide to withdraw from the study, all efforts will be made to report the reason for withdrawal as thoroughly as possible.

There are three withdrawal options:Withdrawing completely (i.e. withdrawal from allocated treatment and consent to follow-up data collection)Withdrawing from active participation in the trial but allowing continued review by the research team of healthcare recordsInvestigator-led participant change in status would be considered for the following reasons: Prophylaxis arm: Unable to tolerate any suitable antibiotic agent or pregnancy.No prophylaxis arm: Change in circumstance whereby starting prophylaxis is an urgent clinical necessity within 6 months of randomisation or pregnancy.

We will encourage participants who decide to withdraw to choose option 2, but if they wish to withdraw completely we will retain data collected up to the point of withdrawal. Participants will be asked if they would be happy for the reason for the decision to withdraw to be recorded. Participants who withdraw completely will not be replaced, but the rate of withdrawal will be monitored and reported to the DMC.

### Statistical analysis

An analysis of the primary outcome measure (incidence of UTI) for the full study will be performed both for the full data set and for the separate sub-groups defined by high and low baseline UTI rate (as specified during stratification for the randomisation process) using both the Poisson rate test and an incidence density ratio approach to allow for the different treatment durations; regression or generalised linear modelling approaches will be used to adjust for the effects of covariates. The model selection process will include the stratification factors (prior rate of UTI, presence of neurological disease and gender) and other baseline variables (person doing CISC [self or other], asymptomatic bacteriuria, age, type of catheter, use of antibiotic prophylaxis for UTI in the previous 12 months prior to randomisation and presence of bladder augmentation). The inclusion of interaction terms such as site will also be explored. The inclusion of baseline values as covariates will additionally enable the examination of possible interactions between effects observed and these values. Not all covariates mentioned above will be included in the final model, but all will be considered during the model selection process.

A number of additional secondary analyses will also be undertaken to examine the secondary outcome variables. Febrile and microbiologically confirmed UTI, asymptomatic bacteriuria and hospitalisation due to UTI will be analysed in a manner analogous to that for the primary outcome. Analyses of other outcomes will use similar regression or analysis of variance/covariance-based approaches as described above to compare between treatment groups while allowing for the effects of covariates. Baseline measures would be included in the analysis, either considered as possible covariates or by exploring changes in outcome measures from baseline. Analysis will be carried out primarily on an intention-to-treat basis, although other exploratory analyses such as per-protocol may also be considered. Data will be analysed at the end of the study; there are no planned interim analyses. Safety data will be regularly and frequently reviewed but will not be subjected to statistical analysis. Data with missing observations due to loss to follow-up will be examined to determine both the extent of the missing data and whether they are missing at random or are informative. If data are missing to a sufficient extent, the use of appropriate multiple imputation techniques will be considered.

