**Methods/design:**

This is a 52-site, patient randomised superiority trial set in routine care comparing an experimental strategy of once daily antibiotic prophylaxis for 12 months against a control strategy of no prophylaxis in people who carry out self-catheterisation and suffer recurrent urinary tract infections. The primary outcome is number of urinary tract infections during a 12-month treatment period. Both groups will otherwise receive usual care including on demand treatment courses of antibiotics for urinary tract infection. Participants and their clinicians will not be blinded to the allocated intervention, but central trial staff managing and analysing trial data will, as far as possible, be unaware of participant allocation. The analysis will follow intention-to-treat principles.

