## Background

Clean intermittent self-catheterisation (CISC) is a frequently used intervention for people who cannot empty their bladder effectively due to bladder outlet obstruction or failure of bladder muscle contraction which may be associated with neurological disease [1]. Patients needing CISC are taught how to insert a catheter, drain the bladder and then remove the catheter [2]. Single-use disposable catheters, typically with a hydrophilic coating, are predominantly used in the UK [3].

There are no accurate prevalence data for CISC use in the UK. The National Health Service (NHS) England prescription database recorded 47 million CISC catheter prescriptions in 2010 at a cost of £64 million [4]. If we assume each individual uses an average of 25 catheters per week, this suggests that there are about 36,000 CISC users in England and perhaps 43,000 in the UK as a whole. This estimate is in agreement with a primary care-based estimate which found a prevalence of approximately 7–8 per 10,000 adults, suggesting an approximate total of 43,000–49,000 adults in the UK ([name], personal communication, August 2011).

Recurrent urinary tract infection (UTI) is the commonest adverse event experienced by CISC users affecting between 12–88 % of studied cohorts [5]. Differentiation between asymptomatic bacteriuria, which would not normally be treated, and symptomatic UTI in these studies is difficult. One estimate suggests that 50 % of users have persistent bacteriuria and at least 25 % suffer two or more symptomatic UTI episodes per year [6]. Conservatively this suggests that up to 10,000 CISC users in the UK suffer recurrent UTI, the target population for this trial. Neurological disease, female sex, young age and high bladder volumes are associated with higher prevalence of UTI [1]. *Escherichia coli* (*E. coli*) is the causative bacterium in 60–70 % of cases [6]. Most episodes are associated with transient symptoms such as lower abdominal pain, urethral pain and flu-like symptoms; occasionally systemic upset can occur with fever and loin pain. Those with reduced bladder sensation may alternatively complain of cloudy urine, increased odour and incontinence [7]. Recurrent UTI is distressing and an additional burden for patients with underlying neurological disease and functional disability [5]. For some there is a risk of renal damage in the longer term [7] or significant sepsis requiring intensive care and potential mortality.

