### Randomisation

#### Participant allocation

Randomisation will be administered centrally by the Newcastle Clinical Trials Unit secure web-based system. Permuted random blocks of variable length will be used to allocate participants 1:1 to the control and experimental groups and ensure concealment of allocation from central trial staff. An individual not otherwise involved with the study will produce the final randomisation schedule. Stratification by three variables: (1) prior frequency of UTI: <4 episodes per year and ≥4 episodes per year, (2) a diagnosis of neurogenic lower urinary tract dysfunction: yes or no and (3) sex: female or male, will be performed prior to randomisation to ensure balanced allocation within these factors. For those allocated to prophylaxis an appointment will be arranged, facilitated by trial staff, with the prescribing clinician to commence prophylaxis. This may be a hospital consultant, a GP or a nurse specialist. Continued supply will be ensured typically through repeat prescription from the individual participant’s GP.

Patients may only be randomised into the study by an authorised member of staff at the study research site, as detailed in the delegation log.

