### Sample size calculation

We plan to recruit 372 participants to the trial. Based on systematic reviews [11, 14] and expert (including patient) opinion, we believe that an overall 20 % reduction in symptomatic UTI rate from an average of 3 to 2.4 episodes per year represents the minimum clinically important difference. Using the Poisson rate test, completion of the study by 158 participants in each arm, 316 in total, would give 90 % power to detect this difference at the 5 % level. A total of 372 would allow for a 15 % attrition rate estimated from previous trials included in the systematic review. The attrition rate will be monitored and the sample size increased if necessary. Half this sample size would give 92 % power to detect a 25 % difference in the high frequency sub-group (from 4 to 3 episodes per year) and more than 99 % power for a 50 % reduction in the low frequency group (from 2 to 1) without allowance for multiple testing. We will approach approximately 750 eligible patients, anticipating a 50 % recruitment rate. We are currently recruiting from 52 sites which are coordinated through seven trial hubs. This number will be adjusted according to site and overall recruitment rate. For the qualitative sub-study of participant perception of benefit we will interview 30 trial participants who, at the time of trial consent, expressed a willingness to be interviewed at completion. We will create a purposive sample of approximately 20 participants from the prophylaxis arm and 10 from the no prophylaxis arm including some with neurological disease and some who did not complete the trial as allocated. We anticipate this will be sufficient to saturate themes arising from qualitative analysis of interview transcripts. For contingent valuation we will use a sample of 100 participants in each group; 200 in total will complete an exit questionnaire.

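### The Poisson rate test named for the primary UTI comparison, and used to size the trial, makes no allowance for between-patient variation in UTI rate that the protocol itself expects

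*Protocol article*

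**What the plan says.** The abstract of the protocol article defines the outcome as a count of repeated events: "The primary outcome is number of urinary tract infections during a 12-month treatment period". The Statistical analysis section says that it will be analysed, in the full data set and in the high and low baseline-rate sub-groups, "using both the Poisson rate test and an incidence density ratio approach to allow for the different treatment durations". It then adds that "regression or generalised linear modelling approaches will be used to adjust for the effects of covariates", without naming a distribution or a variance estimator.

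The Sample size calculation takes a 20% reduction "from an average of 3 to 2.4 episodes per year represents the minimum clinically important difference". It continues: "Using the Poisson rate test, completion of the study by 158 participants in each arm, 316 in total", which "would give 90 % power to detect this difference at the 5 % level".

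On differences between patients, the Background says: "Neurological disease, female sex, young age and high bladder volumes are associated with higher prevalence of UTI". Randomisation is stratified by "prior frequency of UTI: <4 episodes per year and ≥4 episodes per year", by neurogenic dysfunction and by sex. The sample size section expects control rates of 4 a year in the high-frequency sub-group and 2 in the low-frequency sub-group.

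**The concern.** A Poisson rate test compares two totals and takes the variance of each to equal its mean. This is correct only if patients share a common rate, or if all differences in rate are balanced out by the stratification.

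The protocol gives reasons to expect more variation than that:

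- The upper prior-frequency stratum has no ceiling.
- The lower stratum can hold people admitted to the trial on a single hospitalised UTI, on two or three episodes, or after a washout from earlier prophylaxis.
- The analysis section lists further candidate predictors that are not stratified, among them age, catheter type, asymptomatic bacteriuria and bladder augmentation.

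The incidence density ratio is introduced to handle unequal durations, which is a different problem from unequal rates.

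The superiority claim and its confidence interval are at stake. If variation remains within strata, the error goes in one direction: intervals too narrow and false positives too frequent. The article analyses febrile and culture-confirmed UTI and hospitalisation for UTI in an analogous way, so the same choice carries over to them.

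**Working it through.** **1. Reproducing the plan's figures.** Inputs from the Sample size calculation: rates 3.0 and 2.4 a year, 90% power, 5% level (taken as two-sided), 15% attrition. With variance equal to mean:

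n per arm = (1.960 + 1.282)² × (3.0 + 2.4) / 0.6² = 157.6, so 158.

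Then 316 / 0.85 = 371.8, so 372. Half the sample (79 per arm) gives 91.9% power for 4 versus 3 (stated 92%) and 99.9% for 2 versus 1 (stated as more than 99%). A one-sided test would need only 129 per arm. All the stated figures therefore reproduce, with no between-patient variance in them.

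**2. The heterogeneity that the article quantifies.** An equal mix of rates 2 and 4 has mean 3 and variance 3 + 1 = 4, a ratio of 1.33. Without stratification, the Poisson test's type I error would be 2 × [1 − Φ(1.96/√1.33)] = 9.0%. With each arm holding 79 patients at each rate, as stratified allocation would give, 20,000 simulated null trials gave 5.1%. Stratification therefore removes this component.

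**3. Heterogeneity left within strata.** Assumption: patients' true rates vary within each stratum as a gamma distribution with dispersion k. The article gives no value, so a range is shown. Within a stratum of mean m, the variance is m + km². Averaged over the two strata:

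variance/mean = [(2 + 4k) + (4 + 16k)] / (2 + 4) = 1 + 3.33k.

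Type I error = 2 × [1 − Φ(1.96/√(1 + 3.33k))]. The width ratio is the Poisson interval's width divided by the correct width, 1/√(1 + 3.33k).

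| k (assumed) | variance/mean | type I error, formula | type I error, simulated | width ratio |
|---|---|---|---|---|
| 0 | 1.00 | 5.0% | 5.1% | 1.00 |
| 0.1 | 1.33 | 9.0% | 8.9% | 0.87 |
| 0.2 | 1.67 | 12.9% | 12.8% | 0.77 |
| 0.3 | 2.00 | 16.6% | 16.6% | 0.71 |
| 0.5 | 2.67 | 23.0% | 22.5% | 0.61 |
| 1 | 4.33 | 34.6% | 34.6% | 0.48 |

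For scale, k = 0.1 means a standard deviation of about 0.6 around a true rate of 2 (√0.1 × 2 = 0.63). If true rates in the lower stratum were spread evenly over 1, 2 and 3, their variance would be 0.67 and k = 0.67/4 = 0.17. The same k in both strata gives about 12% type I error. In the lower stratum alone the ratio is 1 + 0.33/3 = 1.11, giving about 6%.

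**4. Power of a valid test at 158 per arm.** Put variance m + km² at means 3.0 and 2.4 into power = Φ(0.6 / √(sum of variances / 158) − 1.96):

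- k = 0.2: sum = 4.80 + 3.552 = 8.352, power 74%; 90% power would need 244 per arm.
- k = 0.5: sum = 7.50 + 5.28 = 12.78, power 56%; 90% power would need 374 per arm.

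Here k is the variation left after adjustment, with a single mean rate per arm.

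**5. Why the replacement should adjust for the strata.** In the stratified simulations, an unadjusted test with empirical variance was conservative, at 2.4% for k = 0 and 4.2% for k = 1.

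**The case against.** The strongest reply is that the article does not tie itself to the Poisson test. Two approaches are named, and then a regression or generalised linear model whose family is open. A negative binomial or scaled Poisson model fits that wording. The Study monitoring section refers to a separate analysis plan, which is not at hand and where distribution and variance are commonly settled. This stands in part: silence about overdispersion would not by itself be a fault. But the article is not silent on the test. It names one that assumes there is none, sizes the trial on it, and leaves the regression for covariate adjustment, without saying which result decides.

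Second, two of the four risk factors in the Background (neurological disease and sex) are stratification factors, and age is a candidate covariate. That also stands, and k must be read as whatever is left after all of this. It need not be large.

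Three stronger readings are tempting, but the documents do not support them:

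- A reader might infer that the false-positive rate will be well above 5%. No dispersion figure is given, and the only quantified heterogeneity leaves it near 5% under the planned stratification.
- A reader might infer that the incidence density ratio shares the Poisson variance. No variance formula is given for it. It is no remedy if its interval is Poisson-based, but that is not stated.
- A reader might infer that the economic results inherit the narrow interval. The Economic analysis section plans participant-level costs and stochastic sensitivity analyses, and nothing there draws on the Poisson interval.

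**Conclusion.** The point holds conditionally. The named test has no room for between-patient variation beyond what stratification balances, and the protocol's own text makes some such variation likely. If there is none within strata, the test is sound and the stated power is right. If there is some, type I error exceeds 5%: about 9% at k = 0.1, 23% at k = 0.5 and 35% at k = 1. These values rest on assumed gamma heterogeneity with the same k in both strata, and on equal-sized strata with control rates of 2 and 4. The stated 90% power rests on the same zero-dispersion assumption as the test.

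**What to change.** Name one decisive primary analysis: negative binomial regression of each participant's UTI count, or Poisson regression with robust or Pearson-scaled variance. Adjust it for the three stratification factors and use the log of follow-up time from randomisation as offset. Report the treatment rate ratio with its interval from that model. Keep the Poisson rate test as descriptive only. Use the same approach for the count outcomes that the article analyses analogously to the primary outcome.

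State beside the sample size that 158 per arm gives 90% power only without overdispersion, and show the power for a range of k (for example 74% at 0.2 and 56% at 0.5, both assumed).

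The change is one of wording, made before the analysis, and needs no new data. It does have a statistical price. At k = 0.1 the correct interval is about 1.15 times the Poisson width (1/0.87), and at k = 1 about twice it (1/0.48). The trial may prove less powerful than stated.

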Current evidence for effectiveness of antibiotic prophylaxis by CISC users, the focus for this trial, has been summarised by a Cochrane review updated to September 2011 [14]. We were unable to identify any further published or ongoing trials from that date up to December 2015. The review found six RCTs involving adults (four trials) or children (three trials) performing CISC for neurological bladder dysfunction with a total of 406 participants. Five had placebo as a comparator with either a crossover or parallel group design, and three each used clinical or microbiological definition for UTI outcome; the latest report was 2011. Two of the crossover trials had a duration of 3 months for each intervention without washout whilst one had a duration of 5 months for each intervention and a 1-month washout period. The prophylactic agents used were trimethoprim-sulfamethoxazole (two trials) and nitrofurantoin (four trials) and a variety of agents (one trial). Participant attrition after randomisation ranged from 2–35 %. One trial using the outcome of clinically defined symptomatic UTI found a relative incidence rate (95 % CI) of 0.50 (0.17–1.44) in favour of antibiotic prophylaxis whilst another trial found no difference. For the outcome of microbiologically proven symptomatic UTI, one trial found a relative risk of 0.78 (0.62–0.79) in favour of prophylaxis. Evidence from four trials showed an overall relative incidence rate (95 % CI) for bacteriuria of 0.61 (0.44–0.87) in favour of prophylaxis. The review authors concluded that, although results were promising, there was a lack of unequivocal evidence for effectiveness of antibiotic prophylaxis for CISC users, agreeing with a previous review [15]. Recommendations for future trials were as follows:Use incidence of symptomatic UTI as the primary outcomeMeasure antibiotic resistanceControl for factors increasing UTI risk: sex, frequency of catheterisation, neurological cause, frequency of previous UTI, prior use of antibiotic prophylaxis

None of these trials found any excess harms in the prophylaxis groups, but ecological changes in pathogens were not studied. These results and the need for further trials have been highlighted in a further narrative review [16].

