#### Sources of bias

To allow randomisation, eligible participants and the responsible clinician will both need to be sufficiently uncertain of whether the experimental or control strategy is better for relief of recurrent UTI considering each individual’s particular circumstances. Given the lack of high-level evidence as to which is more effective, we will provide trial information illustrating the uncertainty and the need for a definitive trial. This will act to ensure that any selection bias in terms of characteristics of CISC users willing to be randomised is minimised. An anonymised screening log will be kept at each site listing demographic and clinical characteristics and reasons for declining randomisation (if offered) and used for comparison of this group with those entering and those completing the trial. Secondly the characteristics of participants who cross over at randomisation or at a later stage, withdraw or regret their allocated treatment option may differ from those completing 12 months of their allocated strategy. We will address this by comparison of SF-36 scores between these groups measured at baseline prior to randomisation and following treatment. Trial literature given to all participants and to their clinicians will detail other measures to reduce the risk of UTI such as adequate fluid intake, increased frequency of catheterisation, cranberry products and, if appropriate for post-menopausal women, vaginal oestrogen supplements.

Given the lack of blinding, it is possible that participants allocated to the control of no prophylaxis will be more likely to seek treatment for symptoms suggestive of UTI, and that their clinicians may be more likely to prescribe treatment antibiotic, thus introducing bias to our primary outcome. To reduce the potential for this bias, we will give information on the use of antibiotic treatment, describing indication and choice of agent, in trial literature to participants and their GPs according to established guidance from the British Infection Association (BIA) and other groups. We will also include in the participant information packs advice on when to seek help regarding symptoms suggestive of UTI and the use of simple measures to avoid or avert symptomatic UTI. To ensure uniformity of processing and culture techniques, we will use the results of analysis performed at our central laboratory for trial outcomes. The local result will be used for the study if the central result is missing.

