### Data collection and follow-up

Outcome data will be recorded by the participant on questionnaires, which will be made available in paper-based and electronic format, and on the worksheet by local research staff under a unique identifier with subsequent electronic entry onto electronic case report forms (eCRFs) onto the web-based secure clinical data management system for storage at Newcastle Clinical Trials Unit (CTU). Baseline data will include demographics, underlying disease characteristics, details of catheterisation, prior frequency of UTI and associated usage of healthcare and past urine microbiological reports, together with symptom and QoL measures recorded prior to randomisation. Urine, blood and perianal swab samples will also be collected at baseline for immediate testing and banking of serum, urine and *E. coli* isolates for additional studies. During the 12 months of study participation, participants will be asked to keep a simple log recording episodes of suspected UTI from a symptom and help-seeking point of view. If required, trial staff will contact participants approximately monthly to help complete the UTI logs within a reasonable recall window. The patient logs will be validated if necessary by data from regular inspection of primary and secondary healthcare records for UTI events and subsequent direct checking with participants by their preferred means (telephone, text, e-mail). Other outcome data will be collected by patient questionnaire at 3, 6, 9 and 12 months supplemented by regular inspection of health records. Details of participant progress will be recorded on CRFs. A schedule of events is shown in Table 1.

**Table 1 Tab1:** Schedule of study interventions and outcome data collection from participant

Intervention/data	Visit 1 Initial screen	Visit 2	Visit 3	Visit 4	Visit 5	Visit 6	At time of UTI
		Consent, baseline and randomisation	3 months	6 months	9 months	12 months	
Eligibility checklist	x						
Trial discussed and PIS given	x						
Informed consent		x					
UTI questionnaire		x	x	x	x	x	x
Adverse events			x	x	x	x	x
SF-36		x	x	x	x	x	x
Resource use questionnaire			x	x	x	x	
Patient cost questionnaire						x	
Treatment satisfaction questionnaire						x	
Contingent valuation questionnaire						x	
Catheter specimens of urine (CSU) to central laboratory		x	x	x	x	x	x
Perianal swab		x		x		x	
Creatinine (eGFR) and LFT		x				x	

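### The candidate covariates for the primary outcome model cover four of the five risk factors that the cited review recommends controlling for and leave out frequency of catheterisation without a reason (minor)

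*Protocol article*

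**What the plan says.** The Background section of the Protocol article summarises a Cochrane review and introduces its advice with "Recommendations for future trials were as follows". One item is to control for "factors increasing UTI risk: sex, frequency of catheterisation, neurological cause, frequency of previous UTI, prior use of antibiotic prophylaxis".

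The Statistical analysis section then names the variables for the covariate-adjusted analysis of the primary outcome: "The model selection process will include the stratification factors (prior rate of UTI, presence of neurological disease and gender"), followed by "other baseline variables (person doing CISC [self or other], asymptomatic bacteriuria, age, type of catheter", recent prophylaxis and bladder augmentation. That makes nine. It adds: "Not all covariates mentioned above will be included in the final model, but all will be considered during the model selection process".

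Two other places bear on the point. Under Data collection and follow-up: "Baseline data will include demographics, underlying disease characteristics, details of catheterisation, prior frequency of UTI and associated usage of healthcare". Under Sources of bias, literature for all participants and their clinicians describes "other measures to reduce the risk of UTI such as adequate fluid intake, increased frequency of catheterisation".

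**The concern.** The article reports a list of five factors and then builds a candidate set that covers four of them. The fifth, frequency of catheterisation, is neither a candidate covariate nor one of the three stratification factors in the Randomisation section, and nothing explains why. The article's own advice to participants treats it as something that bears on infection risk.

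If baseline frequency predicts the infection count, leaving it out keeps that variation in the residual of the primary comparison. A chance difference between arms would then go unadjusted unless the candidate set were widened. Widening it after the data have been seen would be open to criticism, so the decision is better written down beforehand.

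**Working it through.** **1. Match the two lists.**

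| Factor recommended by the cited review | Where the plan handles it |
|---|---|
| Sex | Stratification factor and candidate covariate |
| Neurological cause | Stratification factor and candidate covariate |
| Frequency of previous UTI | Stratification factor (below 4, or 4 and above, per year) and candidate covariate |
| Prior antibiotic prophylaxis | Candidate covariate (previous 12 months) |
| Frequency of catheterisation | Not listed |

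**2. Reproduce the plan's sample size.** Inputs from Sample size calculation: rates 3 and 2.4 per year, 90% power, 5% level, Poisson rate test, 15% attrition. Two-sided:

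n = (1.960 + 1.282)² × (3 + 2.4) / (3 − 2.4)² = 157.6, so 158 per arm.

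316 / 0.85 gives 372. Both figures match. The calculation uses an unadjusted test, so the covariate list does not enter it.

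**3. Possible gain in power, first parameterisation.** The documents give neither the between-participant dispersion a nor the share of it that baseline frequency explains, so both are assumptions. With var(log rate ratio) = (1/3 + 1/2.4 + 2a) / 158 and power = Φ(|ln 0.8| / SE − 1.96):

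| Assumed a | Power, frequency omitted | 5% of a explained | 20% of a explained |
|---|---|---|---|
| 0 (pure Poisson) | 90.0% | 90.0% | 90.0% |
| 0.3 | 67.5% | 68.5% | 71.5% |
| 0.5 | 56.4% | 57.6% | 61.5% |
| 1.0 | 39.4% | 40.6% | 44.8% |

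Example, a = 0.3: the variance is (0.75 + 0.60) / 158 = 0.00854, SE 0.0924, and 0.2231 / 0.0924 − 1.96 = 0.45, so power is 67.5%. The gain runs from 0 to 5.4 points. The lower starting powers come from the assumed dispersion, not from the missing covariate.

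**4. Possible gain, second parameterisation.** Assume a rate ratio per standard deviation (SD) of baseline frequency, independent of the listed covariates. Omitting it adds (ln RR)² to the between-participant variance.

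| Assumed RR per SD | Variance saved, no other dispersion | Power gained | Variance saved, other dispersion 0.5 | Power gained |
|---|---|---|---|---|
| 1.05 | 0.6% | 0.2 points | 0.3% | 0.1 points |
| 1.1 | 2.4% | 0.7 points | 1.0% | 0.5 points |
| 1.2 | 8.1% | 2.6 points | 3.7% | 1.6 points |
| 1.3 | 15.5% | 5.5 points | 7.3% | 3.2 points |

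**5. Chance imbalance.** The standardised difference between arms has standard error √(2/158) = 0.1125. The central 95% of imbalances would multiply the estimated rate ratio by exp(±1.96 × 0.1125 × ln RR): 0.989 to 1.011 for RR per SD 1.05, 0.979 to 1.021 for 1.1, 0.961 to 1.041 for 1.2 and 0.944 to 1.060 for 1.3. The target rate ratio is 2.4 / 3 = 0.80. These shifts are another view of the variance in step 4, not an addition to it.

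**The case against.** The strongest reply has four parts.

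- **The analysis plan.** The article says that a documented statistical analysis plan, not shown here, will govern all analyses, and covariate detail often sits there. This stands in part: that plan may already include the variable. But the article names its candidates one by one, with no wording that marks them as examples, so the absence of this one is something the article states.
- **The status of the two lists.** A reader might infer that the trial is bound to control for all five factors, or that the nine variables are the primary model. Neither holds. The five are a cited review's recommendation, and the article does not undertake to follow each one. The nine are candidates for selection, so listing a tenth would not guarantee adjustment.
- **Availability and predictive value.** Frequency is not named among the baseline items; that it falls under catheterisation details is an inference. Advice to catheterise more often concerns a change in behaviour and does not show that the baseline value predicts infections. Needing to catheterise more often is also a listed UTI symptom in the primary outcome, so a straight-line effect is not assured. These points stand, although patients with a current infection are treated and symptom-free before randomisation.
- **Validity.** A reader might infer bias or an underpowered design. Randomisation rules out systematic bias from the omission, the test's error rate already allows for chance imbalance, and the sample size does not use covariates. This stands in full.

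**Conclusion.** The omission is real and unexplained, and it is minor. Its cost is some precision and some protection against chance imbalance in the adjusted analysis: about 0 to 5.5 points of power, and at the strongest association tried, a chance shift of up to about 6% in the rate ratio.

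Those figures rest wholly on an assumed dispersion and an assumed strength of association. They are upper values for each assumption, because prior infection rate and neurological disease may already carry part of the signal. Under the plan's own pure Poisson assumption there is no between-participant variation left to explain, and the gain is zero. The documents do not support saying that a known amount of power has been lost.

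**What to change.** In the Statistical analysis section, and in the analysis plan, name baseline frequency of catheterisation as a pre-specified adjuster of the adjusted primary model, not only as one more candidate for selection. Fix its functional form in advance. Confirm that it is recorded as its own item within the baseline catheterisation details.

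Use only the value recorded before randomisation. The advice on frequency may change it afterwards, and in an open-label trial that change could differ by arm.

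If the trial team prefers to leave the variable out, one sentence giving the reason would close the point.

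The cost is one degree of freedom if it enters as a single term and, if frequency is already recorded, no new data collection. The sample size stays as it is.
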